##### Pharmacoeconomic evaluation

• The pharmacoeconomic evaluation will be performed according to a parallel and independent protocol with special consideration of the direct costs associated with the health care of these patients.

### Study procedures

The various study visits will be distributed as shown in Table
1:

**Table 1 T1:** Study timeline

**Day**	**−3 or −2**	**0**	**3**	**7 (±1)**	**15 (±3)**	**30 (±5)**	**60 (±7)**	**90 (±7)**
Recruitment	**√**							
Informed consent	**√**							
Selection criteria	**√**							
Medical history	**√**							
Physical examination	**√**							**√**
Blood samples for pharmacogenetics	**√**							
Randomization	**√**							
Acenocoumarol dosing (initiation/adjustment)^a^		**√**	**√**	**√**	**√**	**√**	**√**	**√**
INR determination		**√**	**√**	**√**	**√**	**√**	**√**	**√**
Evaluation of side effects		**√**	**√**	**√**	**√**	**√**	**√**	**√**

^a^In order to perform appropriate dose adjustments, additional visits can be scheduled as needed, at the discretion of the clinical researcher.

Preselection phase: The patients with VTE will be identified in the emergency department or hospital ward within the first 48 hours of the VTE diagnosis (PTE and/or DVT) and will be checked to ensure they meet the selection criteria.

Before any specific study procedure is performed, the patient will receive the information verbally and in writing through the patient information sheet. The patient must consent to participation in the study in writing (two copies). The patient will keep a copy of the information sheet and the informed consent once they have been signed. Once patients have been included in the study, the medical monitor will be informed of their inclusion and the randomization envelope will be opened to determine the study group to which they will belong.

Patients who were considered for inclusion but were not admitted to the study will be registered in a patient-log along with the cause for their non-inclusion (lack of informed consent, selection criteria, practical issues, and so on).

Inclusion phase (days −3 or −2): After recording in the case report file (CRF) that the patient meets the selection criteria, the patient's clinical situation will be reviewed and the following information about the medical history will be recorded in the CRF: personal history and anamnesis, including concomitant medication with current dosage and regimen, and complete physical examination which will include height and weight. The patient will also be provided with a card listing basic information about the trial, what to do in the event of severe adverse events and the research team's telephone numbers. The start of the treatment with acenocoumarol will occur on day −3 or −2, according to standard clinical practice. The following dosages will be provided to the researcher as a guideline for the local recommendations: 2 mg a day for patients below 65 years of age and 1 mg a day for older patients or those with risk factors.

Pharmacogenetic specimen collection: During recruitment, a blood sample will be taken from the patient (two tubes of 5 mL EDTA K3) and will be sent by messenger to the laboratory where the patient's genotype will be determined.

The samples do not require special conservation or transportation conditions. In the event that the messenger collects the sample the day after extraction, it is recommended that the blood sample be stored in a refrigerator.

The results will be sent by email within 48 hours. The medical monitor will ensure compliance with these deadlines and will solve any logistical problems that may arise.

Individualization phase:

Day 0:

– Control group: The INR will be determined in a capillary blood sample by means of a CoaguCheck® portable coagulometer (Roche FarmaSA, Madrid, SPAIN), and the acenocoumarol dosage will be determined according to standard clinical practice.

– Intervention group: At this time, the results of the genotyping will have returned and the acenocoumarol dose will be calculated according to the developed algorithm.

Days 3 and 7 ± 1: The INR will be determined (capillary blood sample analyzed with a portable coagulometer) in both groups, and the acenocoumarol dosage will be adjusted if necessary. Control group patients will follow the dosage indications according to the standard clinical practice and visits will be scheduled for day 3, day 7 ± 1 and day 15 ± 3, depending on the length of the hospital stay. Patients included in the intervention group will have their acenocoumarol regimen readjusted according to the developed algorithm and will be scheduled for visits on day 3, 7 ± 1 and 15 ± 3, depending on the length of the hospital stay.

INR measurements will be performed on both groups and additional visits deemed appropriate for good control of the anticoagulation will be arranged. Any changes made to the dosage and all INR measurements will be recorded in the CRF and the medical records.

Visit days 15 ± 3, 30 ± 5, 60 ± 7 and 90 ± 7: During each visit, and after determining the INR (capillary blood sample analyzed with a portable coagulometer), the dosage will be adjusted. The patient's next scheduled visit will be arranged, and an additional visit will be scheduled if necessary. Adverse events will be recorded during all visits, as contained in “Adverse events” section of this protocol. During the final visit, a complete physical examination will also be performed.

### Concomitant medication

– After the diagnosis, as recommended by international guidelines on the treatment of VTE, all patients (both the control and experimental groups) will receive low molecular weight heparins (LMWH) for at least seven days.

– All other medication that the patient is taking will be recorded in their medical history and CRF, as well as any changes they present during the course of the study. We will record the brand name of the medication, the active ingredient, dosage schedule, start or change in treatment, end of treatment and whether there has been any resolution of the problem that caused the start or change of treatment.

As is standard practice, the study's medical researchers will take into account this change in medication when adjusting the acenocoumarol dosage for both the experimental and control group.

### Randomization

The randomization was performed using a masked randomization scheme, in a 1:1 ratio, in blocks of four patients and stratified by center. Based on this scheme, randomization envelopes were created for each center. The patient's code was written on the outside of these envelopes (center and patient codes) and inside the opaque sealed envelope was a card indicating the study group to which the patient was assigned. The envelopes and card were stored in the investigator file.

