### Definition of the intervention

Once included in the clinical trial, patients will be randomly assigned to the experimental or control groups. Initially, all patients will receive treatment with low molecular weight heparins (LMWH) along with the standard acenocoumarol dose established according to age, for a maximum of three days (the time required to obtain the genotyping result). Subsequently, dose adjustment will be different in the two groups:

Patients assigned to the experimental strategy will receive the regimen determined by the pharmacogenetic algorithm, which includes demographic (age, gender, weight and height), clinical (concomitant medication) and pharmacogenetic (polymorphisms of *CYP2C9*, *VKORC1*, *APOE* and *CYP4F2*) variables
[25]. INR is also taken into account.

Patients assigned to the control strategy will receive doses according to the standard procedure in routine clinical practice.

As a guide for handling and adjusting the acenocoumarol dosages, the researchers will be referred to the local guidelines developed in ‘Area 5’ for the management of patients treated with acenocoumarol.

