### Masking

The study is single blind, and under no circumstance does the patient know the group to which they have been assigned. The medical researchers are unaware of the randomization scheme. Although there is a risk of unmasking the patient, and the lack of masking for the physician may affect the evaluation variables, we believe that total masking is not feasible in a study using a pragmatic approach.

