## Trial status

This protocol was authorized on 18 March 2010 by the Spanish Medicine Agency in its initial version, with subsequent changes. The protocol described here corresponds to version 5. The Ministry of Health granted partial support for the implementation of the trial (project TRA-010), and CAIBER (Spanish Platform for Clinical Trials) was responsible for the monitoring and coordination of the trial and also partially financed the implementation of the trial. The first patient was recruited in 21 March 2011 and currently, a total of 85 patients have been included. We plan to continue recruitment until December 2012.

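### The arm is disclosed two to three days before the strategies differ, and a fixed block of four at each center could make late-in-block assignments predictable

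*Protocol article*

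**What the plan says.** All places are in the Protocol article.

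- **Randomization.** Allocation was made "in a 1:1 ratio, in blocks of four patients and stratified by center". Envelopes were prepared for each center and coded outside by center and patient; "inside the opaque sealed envelope was a card indicating the study group to which the patient was assigned". On storage: "The envelopes and card were stored in the investigator file".
- **Study procedures.** Written consent and inclusion come first; then "the medical monitor will be informed of their inclusion and the randomization envelope will be opened to determine the study group". The sentence does not say who opens it. Table 1 puts randomization in the column for day −3 or −2. Patients considered but not admitted are logged with the reason.
- **Definition of the intervention, and Study procedures.** Everyone first receives heparin and an age-based standard acenocoumarol dose for up to three days while genotyping is done. "Subsequently, dose adjustment will be different in the two groups". The start-up doses are described as guidance, and the algorithm dose is first calculated on day 0.
- **Masking.** Only the patient is blind. Researchers are said not to know the randomization scheme, but the section concedes that "the lack of masking for the physician may affect the evaluation variables".
- **Withdrawal criteria.** The investigator may withdraw a patient on his or her own judgment.
- **Statistical analysis.** All recruited patients enter the intention-to-treat analysis, and a patient lost before day 7 is scored as out of range.
- **Trial status.** At the time of writing, "currently, a total of 85 patients have been included".

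**The concern.** There are two separate weaknesses.

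**Timing.** For two to three days the design intends the arms to be treated alike, yet the assignment is already open to an unmasked physician. Nothing in that period requires the arm to be known. The start-up dose leaves room for judgment, as does withdrawal, so both can differ by arm. Early losses also enter the primary analysis as failures of a strategy that had not begun. Equal losses dilute the effect; unequal losses bias it.

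**Predictability.** With one block size within each center and arms visible after assignment, a site that knows or works out the block size can deduce the last place in every block, and sometimes the last two. Whoever recruits could then decide whether to approach a patient in the light of the next arm. Intention-to-treat analysis cannot repair selection that happens before randomization.

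**Working it through.** **1. The plan's own sample size.** Inputs from Sample size calculation: 40% versus 60%, alpha 0.05 (taken as two-sided), power 80%. With pooled variance and no continuity correction:

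n = [1.96·√(2·0.5·0.5) + 0.8416·√(0.4·0.6 + 0.6·0.4)]² / 0.20² = (1.3859 + 0.5831)² / 0.04 = 96.9, so 97 per group.

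This matches. Adding 20% gives 117 (97 × 1.2) or 122 (97 / 0.8), either side of the stated 120. The point does not disturb these figures.

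**2. The common period.** Randomization is on day −3 or −2 (Table 1) and the strategies diverge on day 0 (Study procedures). The gap is two to three days.

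**3. Effect of losses in that gap.** The documents give no loss rate for these days, so the rates below are assumptions. I also assume that withdrawn patients are handled as lost, and that those lost would have had their arm's average result. If a share L is lost in an arm with true rate p, the scored rate is p(1 − L).

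- Equal loss, L = 5%: 0.60 × 0.95 = 57% and 0.40 × 0.95 = 38%, a difference of 19 points.
- Equal loss, L = 10%: 54% and 36%, a difference of 18 points.
- Unequal loss, 4 extra of 120 in the experimental arm: 0.60 × 116/120 = 58.0%, a difference of 18.0 points.
- Unequal loss, 4 extra of 120 in the control arm: 0.40 × 116/120 = 38.7%, a difference of 21.3 points.
- With 2 to 6 extra losses the difference runs from 19.0 to 17.0 points (experimental arm) or from 20.7 to 22.0 points (control arm).

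**4. Predictability of blocks of four.** There are six equally likely orders of AABB. Assume the worst case: the guesser knows the block size, where blocks start and every past assignment at the center.

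| Place in block | Best guess right | Chance that the arm is certain |
|---|---|---|
| 1 | 1/2 | 0 |
| 2 | 2/3 | 0 |
| 3 | (1/3)·1 + (2/3)·(1/2) = 2/3 | 1/3 |
| 4 | 1 | 1 |
| Mean | 2.833/4 = 70.8% | 1.333/4 = 33.3% |

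Pure chance would give 50% and 0%.

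**5. What other block schemes achieve.** Exact enumeration gives, for fixed blocks of six, 25.0% certain and 68.3% guessed; for fixed blocks of eight, 20.0% and 66.6%. For varied, undisclosed sizes I use a simulation of 48 patients per center (240/5, assuming equal centers) in which the guesser always names the arm that is behind:

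- sizes 2, 4 and 6: 70.0% right
- sizes 4 and 6: 69.0% right
- sizes 4, 6 and 8: 67.7% right

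Varying the size mainly hides where a block ends. It hardly lowers the guess rate, and including blocks of two takes away most of even that small gain.

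**6. Patients who could benefit.** 240 − 85 = 155, or 65% of the total, at the time of writing. The number left when an amendment took effect would be smaller and cannot be known from the document.

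**The case against.** The protocol has real safeguards. The envelopes are opaque, sealed and pre-coded. They are opened only after consent and inclusion, with the medical monitor informed. A log of patients not admitted gives a direct check on selective enrolment, and researchers are said not to know the scheme. Physicians are unmasked until day 90 in any case, as a declared pragmatic choice, so two or three more days may seem to add little. The start-up dose is tied to age, which bounds the discretion. Scoring early losses as failures in both arms keeps them in the analysis.

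Much of this stands, and it rules out stronger readings that a reader might infer:

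- *That unmasked physicians open the envelopes.* The text names no one.
- *That allocation is in fact guessable.* That needs the block size to be known or inferred, and the Masking section says the scheme is not known. The 33% and 71% are a ceiling.
- *That the article reveals the block size while 155 assignments remain.* The count of 85 belongs to the time of writing, and no publication date is shown.
- *That early loss biases the result.* Equal loss only dilutes it, and no loss rate is given.

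What the objection does not answer is the timing. The pragmatic argument explains why physicians cannot be masked once the strategies differ; it does not explain disclosure before then. Sealed envelopes and opening after consent prevent peeking and reassignment, but they do not stop someone who has counted past assignments from foreseeing the next one. The log records such selection only if the patient was formally considered.

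**Conclusion.** The point holds as a risk of bias in conduct; it is not an error in any stated figure. The timing is the stronger half because it does not depend on anyone knowing the block size: the arm is disclosed two to three days before it is needed, in a period with discretionary dosing and withdrawal, and with every loss scored as a failure. Its likely size is small, about one point of the 20 for each 5% of equal loss, and a shift of one to two points for four extra losses in one arm. It grows only if losses are numerous or selective. The predictability half is conditional: at most one third of assignments certain and 71% guessed correctly, if a site knows or infers the block size. The existing safeguards reduce that risk without removing it. The change is worth making because it is cheap.

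**What to change.** For the patients still to be randomized:

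1. Reveal the allocation on day 0, after the start-up doses given have been recorded. Blood for genotyping is taken from all participants anyway (Genotyping), so no new procedure is needed. Withhold genotype results from the site until the arm is revealed; otherwise withdrawal could be decided with the genotype known. Define the intention-to-treat set for these patients as all those randomized on day 0, and report earlier departures in the patient flow.
2. Issue new lists by center with randomly varied, undisclosed and larger block sizes, for example 4, 6 and 8, without blocks of two. Hold them off site, with release by the medical monitor, who is already told of each inclusion and already oversees the genotyping deadlines. Expect this to remove most of the certainty about block ends and to lower the guess rate only to about 68%.

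The cost is a short amendment, new lists for five centers, and a statement in the report of when the procedure changed and how many patients were randomized before it. The monitor must be available to release each allocation on day 0, which the document does not confirm. If the 120 per group are counted from day 0, slightly more patients may need to be consented. The sample size itself does not change.

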### Masking

The study is single blind, and under no circumstance does the patient know the group to which they have been assigned. The medical researchers are unaware of the randomization scheme. Although there is a risk of unmasking the patient, and the lack of masking for the physician may affect the evaluation variables, we believe that total masking is not feasible in a study using a pragmatic approach.

### Genotyping

In the recruitment visit, two 3 ml tubes of blood will be collected from all participants for genotyping of *CYP2C9*2* (rs1799853), *CYP2C9*3* (rs1057910), *VKORC1* (*−*1639 G *→* A = rs9923231), *CYP4F2* (rs2108622), and *APOE* (8016 C *→* T = rs7412), using a previously developed multiplex technique
[28]. Measurements will be performed in a centralized manner at the Laboratory of Population Genetics of the Department of Forensics at the Universidad Complutense de Madrid.

### Safety procedures and monitoring of adverse events

#### Anticoagulation monitoring

The INR (International Normalized Ratio) will be determined using a portable coagulometer (CoaguCheck®, Roche FarmaSA, Madrid, SPAIN)) during the visits on days 0, 3, 7, 15, 30, 60 and 90, to verify that the patients are properly anticoagulated and to make the necessary dose adjustments. Dosing adjustments will be performed according to standard clinical practice. For the experimental group, the genetic results will also be taken into account.

If clinically necessary, additional INR measurements and visits will be performed according to standard clinical practice.

#### Laboratory safety determinations

A laboratory analysis including hemogram, biochemistry and coagulation will be performed on the second visit (day 0) and on the eighth or final visit (day 90 ± 7). A hard copy of the results must be signed and dated by the applicant researcher. Results with values outside the normal range will be evaluated by the researching physician who will indicate whether they are clinically relevant or not. Only clinically relevant results will be recorded in the CRF.

Any additional analysis during any of the study visits, requested either by the researcher or other physician, will be recorded in the medical history and CRF along with the reason for the request. A copy of the analysis will be attached to the patient's medical record.

### Adverse events

Any adverse event (not necessarily related to the use of acenocoumarol) will be recorded in the case report form and will be defined as a serious adverse event if it places the patient's life in danger and/or requires or prolongs hospitalization (for example, a major hemorrhagic event).

Hemorrhages will be categorized as major or minor, according to the classification for hemorrhagic events of the International Society on Thrombosis and Haemostasis (ISTH)
[29]. We will use the Naranjo *et al*. algorithm
[30] to determine any causal relationship between the adverse event and the study treatment.

### Withdrawal criteria

The patient can discontinue their participation in the study at any time. The research doctor, in his or her opinion or judgment, may also withdraw a patient from the study if required by the patient's clinical situation or if the patient does not comply with the protocol. The onset of chronic disease during the study will result in exclusion of the subject. The continuation of the patient in the study after the onset of acute disease will be at the discretion of the researcher, taking into account the patient's safety and the influence of the disease and/or its treatment on the evaluation variables.

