### Statistical analysis

All recruited patients will be included in the main analysis, following an ‘intention to treat’ (ITT) strategy. For the ITT analysis, patients lost to follow up will be classified in the following way: 1) patients lost before the seventh day will be considered to be outside the therapeutic range; 2) patients lost before the last visit and that have not reached the stable INR will be considered not to be in stable dosing; 3) all lost visits, the INR will be accounted as being out of the therapeutic range. In addition, we will perform a per protocol analysis on all patients who can be monitored for the three month period planned for the study and who have not missed more than one intermediate follow-up visit.

To compare the analysis variables between both groups, a contrast test of the hypothesis will be appropriate based on the normality of the sample (Kolmogorov-Smirnov test), with a Cox regression for dichotomous variables or Kaplan-Meier curves for representing results whenever possible. A regression model (linear or logistic, as appropriate) will be performed when necessary to correct for possible confounding factors. To determine the difference between the two groups in the proportion of time within the therapeutic range, we will use the linear interpolation method proposed by Rosendaal *et al*.
[27]. Finally, we will perform a regression model stratified by center. The value *P* <0.05 will be established as statistically significant, adjusting for multiple comparisons whenever necessary.

The cost-effectiveness analysis will be performed according to a parallel and independent protocol, with special consideration of the direct costs associated with the health care of these patients.

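### Exclusion for new chronic disease and withdrawal by unmasked physicians are not reconciled with an ITT analysis that scores lost data as out of range

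*Protocol article*

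**What the plan says.** Three rules in the protocol article's Withdrawal criteria act after randomisation:

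- New chronic disease, with no definition or grading, is mandatory grounds: "The onset of chronic disease during the study will result in exclusion of the subject".
- The research doctor "may also withdraw a patient from the study if required by the patient's clinical situation or if the patient does not comply with the protocol".
- After acute disease, continuation is at the researcher's discretion, "taking into account the patient's safety and the influence of the disease and/or its treatment on the evaluation variables".

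The Masking section says that only the patient is blinded and concedes that "the lack of masking for the physician may affect the evaluation variables".

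The Statistical analysis section says "All recruited patients will be included in the main analysis", under an ITT strategy. Three rules then cover patients lost to follow-up. For the day-7 endpoint, "patients lost before the seventh day will be considered to be outside the therapeutic range". A patient lost before the last visit without a stable INR counts as not stable. For "all lost visits, the INR will be accounted as being out of the therapeutic range". A per-protocol analysis is limited to patients who can be monitored for the three months and missed at most one intermediate visit.

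Under Assessment variables, the safety endpoint is the proportion of patients with a relevant event in the first three months. Under Study procedures, adverse events are recorded at visits.

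**The concern.** The withdrawal rules end participation in the study, not merely use of the assigned dosing strategy. The person applying them knows the arm and, after acute disease, may weigh its effect on the endpoints. The analysis section does not say whether an excluded or withdrawn subject is handled as lost to follow-up. If so, a decision made with knowledge of the arm becomes an outcome value: out of range at day 7, not stable, or no in-range INR at later visits.

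The missing values may be obtainable. The Discussion puts recommended VTE treatment at three to six months, and the Anticoagulation monitoring section treats INR measurement as standard practice. A patient given a new diagnosis may therefore still be on acenocoumarol with INRs measured. At stake are the primary endpoints and, to a lesser degree, the completeness of the three-month safety endpoint. An analysis plan cannot repair this later if the INRs were never collected.

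**Working it through.** **Inputs.** From Sample size calculation: in-range rates at day 7 of 40% (control) and 60% (experimental), alpha 0.05, beta 0.2, 97 completers and 120 recruited per group. The documents give no withdrawal rates, by arm or by time. The rates used below are assumptions.

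**1. The plan's own figure.** Two-sided test with pooled variance and no continuity correction:

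n = [1.96·√(2·0.5·0.5) + 0.8416·√(0.4·0.6 + 0.6·0.4)]² / 0.20² = (1.3859 + 0.5831)² / 0.04 = 96.9, so 97 per group. This matches. At 120 per group with no losses, power is 87.7%.

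**2. What the lost-equals-out-of-range rule does at day 7.** Let w be the share of an arm withdrawn before day 7, and r the in-range rate those patients would have had. The arm's observed rate falls by w·r. If they match their arm (r = p), the observed rate is p(1 − w).

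- Control, w = 5%: 0.05 × 0.40 = 0.02, so the difference rises by 2 points.
- Experimental, w = 5%: 0.05 × 0.60 = 0.03, so the difference falls by 3 points.
- If r is anywhere from 0 to 1, the shift for w = 5% lies between 0 and 5 points.

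**3. Equal withdrawal in both arms (40% v 60%, 120 per group).**

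| w in each arm | Observed rates | Difference | Power |
|---|---|---|---|
| 0% | 40% v 60% | 20 points | 87.7% |
| 10% | 36% v 54% | 18 points | 80.4% |
| 20% | 32% v 48% | 16 points | 71.8% |

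With equal true rates, equal withdrawal leaves type I error at 5%. The effect is diluted but the null comparison is not biased.

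**4. Withdrawal in one arm only (40% v 60%).**

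- 10% in control: 36% v 60%, an apparent difference of 24 points.
- 10% in experimental: 40% v 54%, a difference of 14 points and power of 58.5%.

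**5. Type I error with equal true rates and withdrawal in the control arm only.** For a true rate of 40% and w = 10%, the observed rates are 36% and 40%, so d = 0.04.

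- Null SE = √(2·0.38·0.62/120) = 0.0627, and the critical difference is 1.96 × 0.0627 = 0.1228.
- SE of the difference = √[(0.36·0.64 + 0.40·0.60)/120] = 0.0626.
- Upper tail: 1 − Φ[(0.1228 − 0.04)/0.0626] = 0.093. Lower tail: Φ[(−0.1228 − 0.04)/0.0626] = 0.005. Sum: 9.8%.

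| w, control only | True rate 40% | True rate 60% |
|---|---|---|
| 5% | 6.2% | 7.6% |
| 10% | 9.8% | 15.5% |

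**6. INR counts.** The endpoints are numbers of in-range INRs over six weeks and over three months. A lost visit adds zero to such a count whether it is labelled out of range or left missing. For a patient excluded on day 20, the scheduled visits lost are days 30, 60 and 90. Only day 30 falls within six weeks (42 days). The harm here comes from lost data, and the imputation rule adds nothing to it.

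**7. Safety.** The three imputation rules concern INR outcomes only. With events recorded at visits and no follow-up after exclusion described, a first qualifying event after exclusion may go unseen.

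**The case against.** A reader might infer that the withdrawal rules flatly contradict the ITT analysis. The text does not show that. The Withdrawal criteria concern leaving the study, and the Statistical analysis section concerns the analysis set. Nothing says that an excluded subject is dropped from the analysis, and lost patients are explicitly retained by imputation. What stands is that the link between exclusion and loss to follow-up is unstated, and that either reading does harm.

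A reader might also infer that patients excluded after a stroke or myocardial infarction disappear from the safety endpoint. They do not. Both events are components of a per-patient composite, so such a patient already counts, as does anyone with an earlier INR above 4 or below 1.5. Only first events in patients with no earlier qualifying event can be missed. Even that is inferred from visit-based recording, and the full protocol may provide for follow-up after withdrawal.

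The size is hypothetical. The day-7 figures apply only to withdrawals within about ten days of starting acenocoumarol on day −3 or −2, and nothing indicates how many new chronic diagnoses would fall there. That is fair, and it limits the claim to a sensitivity range.

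Finally, the article discloses the lack of physician masking and plans a per-protocol analysis. Disclosure does not remove the mechanism. The per-protocol set leaves out patients not monitored for the full three months, so it gives no independent check.

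**Conclusion.** The concern holds in a limited form. The plan fixes a mandatory post-randomisation exclusion on an undefined condition and allows discretionary withdrawal by physicians who know the arm. It does not say how these patients enter an ITT analysis that scores lost data as failure. The Withdrawal criteria and Statistical analysis sections must be reconciled.

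If exclusion ends follow-up, withdrawal that differs by arm biases the primary endpoints. For the day-7 endpoint the size is 2 to 3 points per 5 points of excess early withdrawal. Type I error is about 6 to 16% for 5 to 10% withdrawal in the control arm only. Both figures assume that withdrawn patients would have matched their arm's in-range rate. The type I error figure also assumes equal true rates of 40% or 60% and 120 per group. Neither the direction of any bias nor the actual withdrawal rates can be derived from the document. The sample sizes are unaffected. This is a cheap and worthwhile improvement, not a demonstrated failure of the trial.

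**What to change.** Amend the Withdrawal criteria and Statistical analysis sections together:

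- State that stopping the assigned dosing strategy, for any reason, does not end follow-up. Clinical decisions on treatment stay with the physician.
- Unless consent is withdrawn, collect INRs and safety events to day 90, from routine care where needed.
- Use the measured INRs in the ITT analysis, and apply the out-of-range rule only where no INR exists.
- Say explicitly how a subject excluded for chronic disease is treated in the analysis.
- Report withdrawals and their reasons by arm.

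The cost is an amendment and some extra case report form work for the patients concerned. Data from patients already excluded may not be recoverable. According to Trial status, 85 of the planned 240 patients had been included, so 240 − 85 = 155 remained to be recruited under the amended rule.
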